### Conduct of analysis and statistical considerations

All statistical analyses will be performed using SAS (SAS Institute) and/or StatXact (Cytel Software Corp) softwares. The results will be reported per dose level/tumour-type cohort and overall.

### Demographic characteristics

Physical examination (age, gender and race), medical history and baseline tumour characteristics will be tabulated and analysed with appropriate descriptive statistics on the *total treated population*.

The *analysis of safety* will be performed on the *total treated population*. All the AEs will be graded according to the National Cancer Institute Common Terminology Criteria for Adverse Events (NCI-CTCAE), Version 4.03 and will be coded to the preferred term level using the Medical Dictionary for Regulatory Activities (MedDRA). A summary of AEs by maximum grade and cohort will be generated. The same analysis will be presented for SAEs and events with a suspected relationship to the study treatment. A summary of AEs by maximum grade and cohort per treatment dose will also be performed. SAEs, DLTs and discontinuation due to AEss will be described in detail by patient narratives.

A summary of the concomitant medications, classified by Anatomical Therapeutic Chemical (ATC) term, will be displayed by cohort. Individual listing of concomitant medications per patient and per time point will also be provided. Finally, the total number of study treatments administered to each patient and the length of active follow-up will be summarised.

The *analysis of clinical activity* will be performed on the *total treated population*, that is, all patients who received at least one NKR-2 treatment (in case of patient’s withdrawal prior the end of the administration phase). Sensitivity analyses related to the clinical activity endpoints will be performed on the *according to protocol* population which includes all evaluable patients who have complied with all the procedures defined in the protocol up to concluding visit.

The first ORR will be assessed at Visit D57. The occurrence and duration of objective clinical response Complete response (CR), partial response (PR) and stable disease (SD) will be reported. Disease progression, including death, during the study will be described. Estimates of the rates of best clinical response and their 95% CIs will be reported. Kaplan-Meier curves will be estimated for PFS and OS.

In addition, other exploratory analyses may be performed, *tha*t is, the clinical activity may be assessed in subpopulations based on the NKG2D ligands tumour expression, types of ligands expressed in tumour, serum levels of soluble NKG2D ligands and so on.

In the dose escalation segment, safety data will be monitored closely on an ongoing basis. The main analysis (leading to the selection of the RecD) will be conducted separately in each arm once all patients in the last dose level have received the three NKR-2 administrations and have completed the safety period (D43). All data related to the primary endpoints of the study will be analysed. The final analysis will be performed once all patients have attended the concluding visit of the follow-up phase (M24) or have been withdrawn from the study.

The expansion segment of the study will proceed in three steps, with a statistical analysis at the end of each step (figure 3). These steps aim to stop the study for futility in specific cohorts or specific tumour types in case of no (sufficient) responders in the corresponding cohorts at the time of analysis.

An interim analysis for futility will be performed on the first 14 patients over all 5 cohorts of patients with solid tumour types and on the first 6 patients over the 2 cohorts of patients with haematological tumour types who have either completed the administration phase (D57) or have withdrawn from the study.

The second step consists in cohort futility analyses after the first seven cancer patients in each tumour type have either completed the administration phase (D57) or have withdrawn from the study. At this step, an evaluation of the safety of the NKR-2 treatment in each cohort will also be performed on the first six patients who completed the 6-week treatment period (D43) or had a DLT. This will allow to adapt the RecD in any specific cohort (tumour type) according to both safety rules and futility analysis. Indeed, if, and as soon as, two or more DLTs have been reported within a specific cohort, and the criterion for futility was not reached, the next patients enrolled in this cohort will be treated at the next lower dose level. In contrast, if no DLT has been reported within a specific cohort, and the criterion for futility was not reached at Step 2, the next patients enrolled will be treated with the next higher dose level.

Finally, the final evaluation of the objective clinical response rate will be evaluated once all the first 14 cancer patients in each cohort have either completed their administration period (D57) or have withdrawn from study due to disease progression or DLT. If, in any cohort, there are >2 out of 14 patients presenting an ORR, the study will be considered as successful in this tumour type.

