**Figure 3 F3:**
[figure not shown]
Overview of the study design. AML, acute myeloid leukaemia; CRC, colorectal cancer; MDS, higher risk myelodysplastic syndrome; MM, multiple myeloma; ORR, objective response rate; RecD, recommended dose; TNBC, triple-negative breast cancer.

The *dose escalation* design will include three dose levels of NKR-2. The assumption is made that the safety profile of the treatment could be different in haematological versus solid tumour types. Therefore, it will be assessed separately in two different arms, one in solid tumours (CRC, urothelial carcinoma, TNBC, pancreatic cancer or epithelial ovarian and fallopian tube carcinoma) and one in haematological tumours (AML/MDS or MM). Each arm will use a 3+3 design to determine the RecD of the NKR-2 treatment for the corresponding cohorts in the expansion segment, as based on the occurrence of DLTs (ie, three patients will be evaluated per dose level for each arm of the segment and three additional patients will be added if one out of three patients in this cohort experiences a DLT to further assess the safety of the treatment). The sample size of the dose escalation part will be between 2 and 18 patients per arm. Six patients will be treated at the MTD (or highest dose level if no DLT was observed).

The RecD will be the MTD unless in case no MTD is determined in the dose escalation segment of the study. In the latter, the RecD will be highest dose evaluated in the dose escalation segment.

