The RecD will be further evaluated in the *expansion segment* of the study to assess separately the safety profile and initial clinical activity of the NKR-2 treatment in seven cohorts of patients with the distinct tumour types (up to 14 patients per tumour type). The expansion segment in haematological and solid tumours will be initiated as soon as their respective dose escalation arm defines the RecD. During this segment, the RecD can still be adapted according to predefined safety rules in any specific tumour type. The statistical analysis is planned in three steps. A futility analysis will be conducted separately in the first 14 patients with a solid tumour and the first 6 patients with a haematological tumour type. These number of patients have been defined to have a 0.05 probability of finding 0 objective response at this step if the true probability of response were 0.2 (solid) or 0.4 (haematological). Subsequently, futility (no response in the first seven patients) and efficacy (three or more responses in 14 patients) will be tested by cohort, based on the Simon’s two-stage optimal design. The assumptions are: type I error rate=0.15, power=0.80 and response probability of poor drug=0.10/beneficial drug=0.30. In total, up to 86 patients are expected to be enrolled in the expansion segment (in addition, the six patients from each arm of the dose escalation segment who were treated at the RecD will be included in these expansion analyses).

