### Treatment regimen

Three NKR-2 dose levels will be evaluated during this study, that is, 3×10^8^, 1×10^9^ and 3×10^9^ NKR-2 for each injection (adjusted to 4.6×10^6^, 1.5×10^7^ and 4.6×10^7^ NKR-2/kg, respectively, for patients with body weight below or equal to 65 kg) with a schedule of administration of three NKR-2 doses administered with a 2-week interval per patient. No systemic lymphodepleting preconditioning will be performed prior to NKR-2 injections.

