### Enrolment rules

There is no requirement for specific recruitment of each individual tumour indication to corresponding arm within the *dose escalation pha*se, but each dose level should enrol at least two different types of cancer. In each arm, patients will be enrolled at the next dose level when all evaluable patients at the same dose level have completed the safety period of 14 days after last NKR-2 injection. Within each dose level, patients will be enrolled as soon as the previous patient has received at least one NKR-2 administration and has completed the 14-day safety period after the first injection.

Enrolment in the *expansion segment* of the study will be performed in three steps, with a statistical analysis at the end of each step (see Adverse events, serious adverse events and dose-limiting toxicities section). Within each step, all patients can theoretically be enrolled at the same time.

Approximately 15 centres are expected to be initiated for patient enrolment in the expansion segment. Recruitment is anticipated to be completed within approximately 24 months. If this target is not met, then the recruitment period may be extended accordingly.

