### Ethics and dissemination

The investigator is responsible for ensuring the study is conducted in accordance with procedures and evaluations described in the clinical protocol. Deviations from the protocol shall not be made without prior approval by the sponsor, except to treat a medical emergency and reduce immediate risk to the patient. In such a case, the investigator shall immediately notify the independent ethics committee (IEC) or institutional review board and the sponsor, according to local requirements.

If changes to the protocol are deemed necessary, a written amendment should be prepared and signed by the investigator and the sponsor and approved by the IEC and applicable competent authorities prior to being implemented.

The *steering committee* will be composed of three members independent of investigators and the sponsor. The role of the steering committee will be to advise on events which may impact the general process of the clinical study. All safety data will be made available to the steering committee in a way that the steering committee can timely advise.

Celyad or designee will host specific *safety data review meetings* (or teleconferences) on a regular basis during the study to discuss and evaluate all of the gathered safety data. This safety follow-up will include teleconference at the end of each dose level of the phase I dose escalation arms and at any new relevant safety event onset (ie, DLT, treatment-related SAE, SUSAR). In addition, members of the steering committee will be requested to review the clinical study report(s) generated from data collected in this study.

*Clinical data review meetings* will be performed at the different study interim analyses for futility by the Celyad clinical trial team and the steering committee in specific. At the time of the interim analyses, the best overall response for each patient will be derived from the overall lesion response assessments recorded in the eCRF. This will be used to calculate the ORR in the respective group(s).

For the purpose of compliance with Good Clinical Practises (GCP) and competent authorities guidelines, it may be necessary for the sponsor or a competent authority to conduct a site audit. This may occur at any time from start to after conclusion of the study. Therefore, when an investigator signs the protocol, he agrees to permit drug competent authorities and the sponsor audits, providing direct access to source data/documents.

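### The Step 2 upward dose rule has no cap: where the recommended dose is an MTD below 3×10^9, a DLT-free cohort is sent to the level its own arm placed above the MTD

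*Protocol article*

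**What the plan says.** **Choice of dose.** The section THINK study design gives each arm (solid, haematological) its own 3+3 escalation: "The RecD will be the MTD unless in case no MTD is determined in the dose escalation segment of the study". If there is no MTD, the rule is: "In the latter, the RecD will be highest dose evaluated in the dose escalation segment". Under Treatment regimen, "Three NKR-2 dose levels will be evaluated during this study": 3×10^8, 1×10^9 and 3×10^9 per injection.

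**Adaptation in the expansion segment.** THINK study design announces it: "During this segment, the RecD can still be adapted according to predefined safety rules in any specific tumour type". The rules themselves are under Conduct of analysis and statistical considerations, in the text below the subheading Demographic characteristics. At Step 2 the first seven patients of a cohort are assessed for futility (no response) and the first six for DLTs. Two or more DLTs without futility lower the dose by one level. With no DLT and no futility, "the next patients enrolled will be treated with the next higher dose level".

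**Oversight and pace.** Ethics and dissemination says that clinical data review meetings with the steering committee "will be performed at the different study interim analyses for futility". It describes the committee's remit thus: "The role of the steering committee will be to advise on events which may impact the general process of the clinical study". Enrolment rules adds: "Within each step, all patients can theoretically be enrolled at the same time".

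**The concern.** The upward rule is worded as an obligation and sets no ceiling. Three situations are possible.

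1. The RecD is an MTD of 3×10^8 or 1×10^9. The next level is then the one the arm's own 3+3 placed above the MTD.
2. The RecD is 3×10^9. No higher level exists and the rule does nothing.
3. Escalation ended below 3×10^9 without an MTD. The next level is merely untested.

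Only the first is at issue, and it is the rule's main field of operation. There, about six DLT-free patients of one tumour type at the lower dose move the rest of the cohort, up to 14 − 7 = 7 patients, to a dose the arm has rejected. Their experience gives no direct evidence on that dose.

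The stated protections do not close the gap. The steering committee can review the data before the increase, but its role is advisory and its approval is not made a condition. Elsewhere the article does name such approvals: Toxicity management mentions those of the steering committee and the sponsor when a postponed treatment is resumed at the investigator's discretion. Interruption at a DLT and the two-DLT lowering rule take effect only after patients have been exposed, and patients within a step may be enrolled together.

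**Working it through.** **The plan's own figures.** The disputed rule carries none. The design around it reproduces:
- Simon design (stop at 0/7, success at 3 or more of 14): exact type I error 0.146 at a response rate of 0.10, power 0.810 at 0.30 (stated 0.15 and 0.80).
- Step 1: 0.8^14 = 0.044 and 0.6^6 = 0.047 (stated 0.05).
- Expansion total: 7×14 − 12 = 86.

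**Trigger chance per cohort, given situation 1.** DLT rates *p* at the RecD are assumptions. Response rates *r* of 0.10 and 0.30 are the Simon design values.
- P(0 DLT in 6) = (1 − p)^6 = 0.531, 0.335, 0.178 for p = 0.10, 0.167, 0.25.
- P(at least 1 response in 7) = 1 − (1 − r)^7 = 0.522, 0.918 for r = 0.10, 0.30.
- Under independence the trigger chance is the product, for example 0.531 × 0.522 = 0.277.

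Two refinements, both lowering the result:
- *Association.* Toxicity management expects cytokine release syndrome to track both efficacy and toxicity. Take an assumed odds ratio of 5 between DLT and response, and let r0 be the response rate without a DLT. The chance becomes (1 − p)^6 × [1 − (1 − r0)^6 (1 − r)]. For p = r = 0.10, r0 = 0.078 and the result is 0.238.
- *Step 1.* Assume 3 of the first 14 solid or 3 of the first 6 haematological patients come from the cohort, and the m others (11 or 3) respond at rate r. Subtract (1 − p)^6 × (1 − r0)^3 (1 − r)^m × [1 − (1 − r0)^3 (1 − r)].

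Results for p = 0.10 / 0.167 / 0.25:

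| r | Independent | Odds ratio 5 | Plus Step 1, solid | Plus Step 1, haematological |
|---|---|---|---|---|
| 0.10 | 0.28 / 0.17 / 0.09 | 0.24 / 0.14 / 0.07 | 0.20 / 0.11 / 0.05 | 0.15 / 0.08 / 0.04 |
| 0.30 | 0.49 / 0.31 / 0.16 | 0.47 / 0.29 / 0.15 | 0.47 / 0.29 / 0.15 | 0.42 / 0.25 / 0.13 |

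**How often situation 1 arises.** Exact enumeration of a usual 3+3: a level passes at 0/3 or 1/6, with probability (1 − p)^3 + 3p(1 − p)^2 × (1 − p)^3. The final RecD is filled to six patients and must show at most 1 DLT, otherwise the dose drops one level. The unconditional trigger is the sum over levels 1 and 2 of P(RecD = k) × (1 − p_k)^6, times P(at least 1 response in 7). For the 5/10/20% curve the sum is 0.0976 × 0.735 + 0.2972 × 0.531 = 0.230. Totals are taken before rounding.

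| Assumed DLT rates, levels 1/2/3 | P(RecD = level 1) | P(RecD = level 2) | P(situation 1) | Sum with 0/6 DLT | Trigger, r 0.10 to 0.30 | With both refinements |
|---|---|---|---|---|---|---|
| 1/2/5% | 0.005 | 0.033 | 0.037 | 0.033 | 0.017–0.030 | 0.011–0.030 |
| 2/5/10% | 0.027 | 0.110 | 0.137 | 0.105 | 0.055–0.096 | 0.033–0.094 |
| 5/10/20% | 0.098 | 0.297 | 0.395 | 0.230 | 0.120–0.211 | 0.066–0.204 |
| 10/20/33% | 0.288 | 0.381 | 0.670 | 0.253 | 0.132–0.232 | 0.066–0.220 |

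The last column runs from the lower haematological to the higher solid value.

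**Which six patients.** Six new patients are assumed in the safety look. If the six escalation patients at the RecD were used instead, the chance of 0 DLT given situation 1 would be 0.90 / 0.79 / 0.64 / 0.49 across the four curves, against 0.89 / 0.77 / 0.58 / 0.38 for new patients. The trigger would not fall.

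**What 0 of 6 shows.** The one-sided 95% upper limit for the DLT rate at the lower dose is 1 − 0.05^(1/6) = 0.39.

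**The case against.** - **The cap may be in the full protocol.** The article is condensed and refers to predefined safety rules. That is possible, but the article prints the rule with its trigger and a mandatory action. If a cap exists, the article misstates the rule.
- **The 3+3 rejection criterion is not spelled out.** Correct: only the expansion to six after one DLT in three is given. That the next level failed on DLTs rests on the usual criterion. A level above a declared MTD is nonetheless not the tolerated one.
- **The upward step may be deliberate.** The arm MTD pools up to five solid or two haematological tumour types, and each dose level must include at least two cancer types. The DLTs behind a rejection may have come from another tumour type. This is the best counter-argument, and adaptation by tumour type is plainly intended. It could support a controlled re-exploration. It does not support an automatic return to a rejected dose on evidence from a lower one.
- **The expected harm is small on these curves.** The mean true DLT rate at the rejected level in situation 1 is about 0.05, 0.09, 0.18 and 0.27. With seven patients at the higher level, independence, and neither Step 1 stopping nor dose lowering, expected excess DLTs per cohort are about 0.003–0.006, 0.02–0.03, 0.07–0.12 and 0.10–0.18. This stands for the curves shown; steeper ones would give more. The article's projected human MTD of 4.3×10^9, scaled from mice, lies above the top level, so the flattest curve cannot be excluded.
- **Safeguards exist.** Interim review can precede the increase, safety meetings follow any DLT, and the dose is lowered as soon as two DLTs occur. These limit the damage, but none of them stops the first exposure.

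**Conclusion.** The concern holds and should be fixed. As printed, the Step 2 rule obliges a DLT-free, non-futile cohort to move to a level that its own arm placed above the MTD whenever the RecD is an MTD below 3×10^9. The logic needs only the article's text and the usual reading of a 3+3.

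How often this would happen depends on assumed DLT rates. Given such an MTD, the refined per-cohort trigger chance is 0.04 to 0.47; without that condition it is 0.01 to 0.22. These figures measure how often the rule would fire and are not estimates of harm. Confidence is medium, because the full protocol may contain an exclusion that the article omits.

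**What to change.** Amend the Step 2 rule to read, in substance: a cohort with no DLT that is not futile stays at the RecD; the dose may rise only to a protocol-defined level, at most 3×10^9, that did not exceed the MTD criterion in that arm's escalation segment.

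This takes one sentence in a protocol amendment. It needs no extra patients or procedures, and leaves the 7/14 Simon design and the total of up to 86 unchanged. The real cost is that the upward step then operates only where escalation ended below 3×10^9 without an MTD. Re-exploring a rejected dose in one tumour type would need its own amendment. If the full protocol already excludes rejected levels, correcting the article's wording is enough.

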### Correlative studies

Peripheral blood samples, bone marrow aspirates from patients with haematological malignancies, as well as tumour biopsies from patients with solid malignancies, will be collected at regular time points during the study (see figure 4) and used to determine NKR-2 persistence post-infusion (using a VCN test) and assess the presence of RCR. Systemic cytokine levels in peripheral blood and levels of tumour-related biomarkers (in the serum, bone marrow or urine samples) will also be assessed to determine whether correlates of NKR-2 activity can be identified. Evaluation and characterisation of the NKR-2 mode of action involving the characterisation of the pre-existing and post/during therapy humoural and cellular immune responses will be done on blood samples collected at baseline and post-NKR-2 infusion. Finally, the correlation with the tumour expression of NKG2D ligand in tumour tissues or cells (type and level) and NKR-2 activity, the characterisation of the TME, the NKR-2 infiltration and the modulation of the local tumour environment of this new type of T cell therapy will be evaluated.

### Toxicity management

As previously mentioned, the use of CAR T cells is limited by potentially severe toxicities, including CRS, neurotoxicity and tumour lysis syndrome (TLS), on-target off-tumour toxicity (related to recognition of the target antigen on normal tissues), clonality and insertional oncogenesis, vector persistence and immunogenicity. While these events may have been seen in relation with other CAR T cell therapies, and are provided for information, there are currently no events considered as expected for NKR-2 therapy (which can be different from other CAR T cell studies based on the unique mode of action) and all serious adverse reactions (SARs) will be considered as suspected unexpected SARs (SUSARs).

The management of toxicities related to CAR T cell therapies was described elsewhere^11 12 55^ but is evolving with everyday new information available from ongoing studies. Sites will be kept informed all along the study for any new therapeutic options modifications or standardisation between the different sites.

Briefly, CRS toxicity is currently of highest concern in the field. It is caused by a release of inflammatory cytokines such as interleukin (IL)-6, IL-2, Interferon (IFN)-γ and Tumour Necrosis Factor (TNF)-α, following the recognition of the target antigen, resulting in a systemic inflammatory response similar to sepsis. Therefore, CRS will correlate with both efficacy and toxicity in patients receiving T cell-engaging therapies. Tocilizumab (anti-IL-6) will be used as the first-line agent in the treatment of CRS. If the patient’s condition does not improve or stabilise within 24 hours of the tocilizumab dose, administration of a second dose of tocilizumab and/or a second immunosuppressive agent (such as corticosteroids) will be considered, based on the CRS revised grading system created by Lee *et al*^56^ to identifying severity and implementation of optimal care strategies for CRS.

TLS resulting in renal insufficiency, rapidly rising uric acid level or evidence of organ dysfunction will be managed with fluids and rasburicase as needed and as determined by the treating physicians.

Further, as NKG2D ligands may be upregulated on stress signals, expression of ligands on non-cancer cells can be expected in tissues that are actively infected or inflamed or experienced cell stress of other aetiology. Infections could therefore invoke a significant inflammatory response by NKR-2 by potentially inducing a CRS due to the increased recognition of ligands by NKR-2 cells. Therefore, any inflammation, infection, concurrent or previous treatment with anticancer therapies will be carefully registered and any Grade 2 or higher autoimmune toxicity will be closely followed to detect any evidence of on-target off-tumour toxicity. Evidence of acute infection, as well as fever of 38°C/100 °F or above, will be therefore considered as an exclusion criterion at screening (see box) or postponement criterion when observed during the treatment phase. In the latter, all study procedures and treatment administration will be resumed where it was left as soon as the patient’s condition allows (within 4 weeks after the scheduled treatment date) or at the investigator’s discretion after steering committee and sponsor approvals.

Since NKR-2 construct consists entirely of human sequences, it is not expected to result in immunogenicity sometimes observed with other CARs using scFv from murine origin (see section Introduction), and therefore multiple NKR-2 injections are allowed without the anticipated risk of humoural immune responses.

Uncontrolled expansion and proliferation of the transformed cells increase the risks for onset of CRS and other CAR-associated toxicities. However, in contrast to more classical CAR T cell therapies, NKR-2 demonstrated neither significant in vivo expansion nor long-term persistence until now,^39^ but since this is the first trial with NKR-2 administrated as multiple doses, the persistence of NKR-2 will be nevertheless carefully monitored post-infusion as mandatory exploratory research. If uncontrolled T cell proliferation occurs (Grade 3 or 4 toxicity related to NRK-2), and as it was reported that CAR-associated toxicity responds to systemic corticosteroids, patients may be treated with corticosteroids and/or chemotherapy to eradicate the CAR T cells.^57^ Patients will be treated with pulse, followed by a rapid taper.

Finally, following FDA recommendation for retroviral and lentiviral vector based gene therapy products, the patient monitoring schedule will also include analysis of the RCR of patient samples up to 15 years after CAR T cell injections.

